## Abstract

Introduction: Temporomandibular joint (TMJ) osteoarthritis is a degenerative disease of the TMJ. It is characterized by progressive degradation of the extracellular matrix components of articular cartilage, with secondary inflammatory components leading to pain in the temporomandibular region and reduced mouth opening. Current treatments do not halt disease progression, hence the need for new therapies to reduce inflammation and, consequently, improve symptoms. The aim of our randomized controlled clinical trial protocol is to investigate the efficacy of adjuvant intra-articular injections of autologous tissue-like stromal vascular fraction (tSVF), compared to arthrocentesis alone, in reducing pain and improving mouth opening in TMJ osteoarthritis patients. Materials and Methods: The primary endpoint analysis will consist of the visual analogue scale (VAS) for pain. The secondary endpoint analyses will include maximal interincisal mouth opening measurements; assessment of oral health and mandibular function based on the oral health impact profile (OHIP) questionnaire and mandibular functional impairment questionnaire (MFIQ); complications during the follow up; synovial cytokine analysis at baseline and after 26 weeks; and nucleated cells and tSVF (immuno)histochemistry analyses of the intervention group. Discussion: Our randomized clinical trial protocol will be applied to evaluate the efficacy of a new promising tSVF injection therapy for TMJ osteoarthritis. The safety of intra-articular injections of tSVF has been proven for knee osteoarthritis. However, since a tSVF injection is considered a heterologous application of cell therapy, the regulatory requirements are strict, which makes medical ethical approval challenging.

## 1. Introduction

Temporomandibular joint (TMJ) osteoarthritis is a degenerative disease of the TMJ. Women, especially menopausal women, are more likely to contract TMJ disorders than men (2:1) [1,2,3,4,5]. Several other non-inflammatory TMJ disorders, such as masticatory muscle pain or headaches, may also cause pain in the temporomandibular region and/or reduced mouth opening and thus demand appropriate diagnosis and therapy. The condition is characterized by progressive degradation of the extracellular matrix components of articular cartilage, with secondary inflammatory components leading to pain in the temporomandibular region and reduced mouth opening [6]. Multiple proteolytic enzymes such as proteases and cytokines (e.g., interleukin-1 (IL-1)) are involved in this cartilage degradation process [7].

The current management of TMJ osteoarthritis is based on non-invasive and invasive therapies. Current non-invasive therapies include occlusal splints, pain medication (such as NSAIDs, e.g., COX-2 inhibitors), as well as physical and psychological therapies [8,9,10]. If these non-invasive options do not reduce symptoms after 2–3 weeks, arthrocentesis, a minimally invasive therapy with or without corticosteroids/hyaluronate injections, should be considered. It involves the lavage of the upper or lower joint space using two communicating needles that are introduced into the upper compartment of the jaw. Invasive treatment options, including open joint surgeries, should be considered for severe cases with severe pathology, pain, and dysfunction [9]. A systematic review of randomized controlled trials of lavage therapy versus nonsurgical therapy in the treatment of arthralgia found that the former is slightly more effective at reducing pain [11]. A subsequent randomized controlled trial confirmed these results and even found that undertaking lavage therapy as the initial treatment reduces pain and functional impairment more rapidly than nonsurgical therapy [12,13]. The relative rapid improvement after arthrocentesis can be explained by the immediate removal of deleterious inflammatory cells and their secreted products such as pro-inflammatory cytokines, matrix-degrading enzymes, reactive oxygen species, and degeneration products, as well as molecules like prostaglandin E2 (PGE2). On the other hand, activated synoviocyte cells remain but might become quiescent due to the lack of chronic pro-inflammatory stimulation. Hence, arthrocentesis gives the joint a head start in the recuperation process. Arthrocentesis also increases mandibular mobility by removing intra-articular adhesions, eliminating the negative pressure in the joint, which reduces the mechanical obstruction [9,12]. While current treatments are symptom-based, the ultimate curative treatment would be to reverse the degeneration process, i.e., to regenerate the lost cartilage in the joint. However, such a curative treatment does not yet exist. The first step in these new therapies would be to stop the degenerative process. Inflammation has been correlated with the progression of TMJ osteoarthritis [14]. It is therefore necessary to develop an effective therapeutic agent that stops the degenerative process by suppressing inflammation and thus also reducing pain. Therapies halting disease progression could be especially effective in the early stages of TMJ osteoarthritis before most of the cartilage has been broken down.

While adipose tissue is already being used in open-joint TMJ reconstructions, a new autologous cell therapy for knee osteoarthritis, namely adipose-derived stromal vascular fraction (SVF) injections, has proved effective in improving pain and range of motion [15]. TMJ osteoarthritis and knee osteoarthritis are considered as low-inflammatory arthritic conditions, with increased pro-inflammatory cytokines in the synovial fluid such as IL-1beta, IL-6, TNF-alpha, and PGE_2_ (Figure 1) [9,16,17,18]. The presence of PGE_2_, one of the most important molecules that induces neuropathic pain [19,20], is more than 4-fold higher in TMJ than in knee osteoarthritis [18]. Synovial fluid analyses one year after an SVF injection showed reduced concentrations of pro-inflammatory molecules (matrix metalloproteinase-2 (MMP-2), IL1-beta, IL-6, and IL-8) and increased concentrations of anti-inflammatory molecules (insulin growth factor-1 (IGF-1) and IL-10) in knee osteoarthritis cases [21]. Anti-inflammatory therapy, such as SVF, is therefore needed for TMJ osteoarthritis to downregulate pro-inflammatory molecules, such as PGE_2_, to reduce pain symptoms. When adipose tissue is mechanically fractionated, this results in a tissue-like stromal vascular fraction (tSVF) [22]. tSVF has been extensively studied for its anti-inflammatory action [23]. In vitro TNFα-treated chondrocytes showed reduced IL-1β and COX2 gene expression after being co-cultured with tSVF-derived cells and conditioned medium [24]. A co-culture of SVF and TMJ-derived synoviocytes that had been exposed to osteoarthritis showed significantly more downregulated inflammatory molecules such as PGE_2_ and CXCL8/IL-8 compared to a synoviocyte monoculture [25].

Recently, the first two human case studies and a trial were published in which processed adipose tissue was injected into the joints of subjects with TMJ osteoarthritis and TMJ disorder [26,27,28]. These studies applied the processed adipose tissue using the nanofat procedure, the MyStem kit, and Lipogems technology, respectively [29,30,31]. They did not note any adverse events and reported reduced pain and improved mouth opening. However, the methodological quality of the two case studies was low because there were no controls. Our hypothesis is that using adjuvant tSVF with arthrocentesis therapy will inhibit the inflammatory response through the release of more anti-inflammatory factors than with arthrocentesis alone and that this will result in less pain and better mandibular function. A well-designed clinical trial is therefore warranted to investigate the effects of tSVF on TMJ osteoarthritis. Thus, the aim of this clinical trial is to investigate the efficacy of adjuvant autologous tSVF intra-articular injections compared to arthrocentesis alone to reduce pain and to increase mouth opening in TMJ osteoarthritis cases.

## 2. Methods and Design

### 2.1. Objectives

The overall aim of this prospective clinical trial is to investigate the efficacy of injecting tSVF intra-articularly to reduce pain and increase mouth function in TMJ osteoarthritis cases. The primary endpoint analysis will be the VAS. The secondary evaluated endpoints for the intervention group will be as follows: maximal interincisal mouth opening, oral health, and mandibular function based on the patient’s oral health impact profile (OHIP) questionnaire and the mandibular functional impairment questionnaire (MFIQ); complications during the follow-up; synovial cytokine analyses at baseline and after 26 weeks; and nucleated cells and SVF (immuno)histochemistry analyses.

### 2.2. Protocol and Registration

Our study is pending approval from the Dutch Central Committee for Clinical Research (CCMO).

### 2.3. Trial Design

This study is planned as a prospective double-blind randomized sham surgery controlled clinical trial. It will be an intervention study with a parallel design consisting of even treatment allocations (ratio of 1:1). All consecutive patients visiting the Department of Oral and Maxillofacial Surgery at the University Medical Center Groningen, The Netherlands, with osteoarthritis of the TMJ will be assessed for eligibility based on the inclusion and exclusion criteria mentioned in Table 1. It is estimated that acquiring the required number of patients suitable for inclusion will take around 1–2 years. The follow-up period will be 1-year post-intervention.

Patients will be included in the study after being evaluated by an oral and maxillofacial (OMF) surgeon who will then schedule them for baseline assessments by the investigator of pain, maximal interincisal opening (MIO), and collection of all the questionnaires (VAS, MFIQ, OHIP-49, SCL-90). The investigator will be blinded regarding treatment allocation during the entire study. After the baseline assessment, randomization will take place (minimization randomization; ALEA, Abcoude, The Netherlands). Both groups will be scheduled for an intervention at the Oral Maxillofacial Surgery outpatient clinic of the University Medical Center Groningen, The Netherlands. An envelope with the treatment allocation will only be handed to the OMF surgeon on the day of surgery.

The patients will not be informed about the treatment allocation. However, since the intervention group will receive an additional liposuction procedure, they could derive their treatment allocation from this additional procedure. Hence, a sham liposuction procedure will be performed on the other group’s patients by preparing a sterile surgical field on the abdomen, making a small stab incision, and then putting a medical plaster on the incision site. The control group patients will be informed about possible liposuction-related symptoms in the same manner as the intervention group patients receiving the actual liposuction. We will not perform the complete liposuction procedure in the control group for ethical reasons. Since the OMF surgeons perform the surgery, they will be informed about the treatment allocation.

Both groups’ post-operative follow-up examinations will be conducted at 3, 12, 26, and 52 weeks (Figure 2). Clinical care-as-usual examinations will be performed by the OMF surgeon to evaluate possible complications. Subsequently, measurements will be taken by the investigator in a separate consultation on the same days as the post-operative examinations.

### 2.4. Participants

In this study, we will ask patients to participate in our research after two consultations (Figure 3). The patients visiting the OMF surgery clinic with TMJ pain symptoms will first be given NSAIDs for 2 weeks. Based on the TC/TMD criteria, arthralgia can be diagnosed by both anamnestic history and exam [32]. To confirm arthralgia, a diagnostic anaesthetic (Ultracaïn forte, 1 mL, Aventis Pharma, Hoevelaken, The Netherlands) will be injected locally into the TMJ. If the pain disappears after this injection, it will be confirmation of TMJ intra-articular pain [33]. Hence, only those with a nociceptive temporomandibular pain disorder will be included in this study. Patients with chronic pain disorders, neuropathic pain, and parasympathetic pain will not respond to the local anaesthetic injection, and so will not be included in this study. At the subsequent 2-week consultation, the responsive patients will be informed about our prospective clinical study and asked if they want to participate. The patient will have two weeks to consider participating.

### 2.5. Surgical Procedure to Obtain and Inject Autologous tSVF

The intervention patient’s donor site (abdomen) will be infiltrated with tumescent solution (5 mL lidocaine 2% in 45 mL of lactated Ringer solution). In total, around 20 mL of lipoaspirate will be harvested from the lateral suprapubic abdominal region by applying manual suction pressure on a Sorensen cannula (Tulip Medical, San Diego, CA, USA) to generate 2 mL tSVF. One millilitre of the solution will be injected into the TMJ upper joint space while the other one millilitre will be subjected to laboratory analyses for quality control purposes.

The fractionation of adipose tissue (FAT) procedure will be executed according to the methods in our previous publication [34]. The procedure will be performed in one of the outpatient clinic treatment rooms of the department of Oral and Maxillofacial surgery at the University Medical Centre Groningen, The Netherlands. A biological safety cabinet will be used to process the tSVF harvested from the patient’s adipose tissue.

Under local anaesthesia, after locating the superior joint space, an 18-gauge needle will be introduced into all the patients’ mandibles at the level of the articular fossa. Usually, the patient senses a forward pressure in the mandible confirming the needle is in the desired location. This can be confirmed further by the backwash principle: fluid coming out of the joint space (i.e., for aspiration purposes from the joint space). Next, a maximum amount of 2 mL saline solution will be injected into the superior joint space, whereupon the patient will be asked to protrude and lateralize the mandible as much as possible and then to try and close the mouth. The syringe will be disconnected from the needle so as to eject the aspired saline solution from the syringe to send for laboratory analysis to determine cytokine concentrations. Then, more saline solution will be introduced into the superior joint space, raising the intra-articular pressure, and the patient will be asked to open their mouth slowly. Subsequently, the syringe will be disconnected from the needle, and the patient will have to close their mouth, which will cause the saline to be ejected through the needle. This step will be repeated two to three times, whereupon the patients’ mandible will be manipulated in forced maximal opening [35]. Finally, 1 mL of the intervention group patients’ own tSVF will be inserted through the same needle into their articular upper space. The control group patients will receive 1 mL of saline.

### 2.6. Outcome Measurements

Pain will be measured with the VAS. Secondary analysis will be performed by measuring mouth opening with a calliper by measuring maximal interincisal opening of the mandibular handicap with the Mandibular Functional Impairment Questionnaire (MFIQ) [36]. Oral health will be evaluated by the Oral Health Impact profile (OHIP-49) questionnaire [37]. The Symptom Check List (SCL-90) will be used to evaluate psychological well-being [38].

From each patient, 1 mL of tSVF will be fixed in 2% paraformaldehyde (PFA) for histological quality control of tSVF. Thin sections (4 µm) of paraffin-embedded tSVF will be deparaffinized and stained with Masson’s Trichrome, Safarin O, and Toluidine staining. Immunohistochemical staining will be performed for caspase 1, perilipin A, and vWF.

At baseline, synovial fluid will be collected during arthrocentesis, and after 26 weeks, an additional arthrocentesis will be performed to acquire synovial fluid for analysis in both the control and intervention group. Synovial fluid will be analysed with a Luminex assay containing pro- and anti-inflammatory factors, including TNF-alpha, IL-1beta, IL-6, IL-8, IFN-gamma, PGE_2,_ FGF, VEGF, IGF, HGF, and MMP-2.

### 2.7. Safety

Risks can be related to the surgical procedure or related to the injected product.

The injection of tissue into the intra-articular space can inflict the risk of infection. However, we will minimize procedure-related risks by producing tSVF in a biological safety cabinet. We will also conduct sterility testing on part of the tSVF that is prepared for injection. If the initial SVF was contaminated, we will then strictly follow these patients. If during the liposuction or isolation procedure of SVF the injected product becomes contaminated, this can lead to a septic arthritis of the TMJ. We have tested our FAT procedure in the operating room, and we have found no contamination due to our procedure (see IMPD). Septic arthritis can be managed by a regimen of non-steroidal anti-inflammatory agents, antibiotics, and arthrocentesis [39]. During the arthrocentesis, the infected tissue can be removed and will be sent to the laboratory for microbial analysis. After this tissue has been removed, the joint can be flushed with saline to alleviate any remaining pressure. When the microbial analysis is finished, a more specific antibiotic therapy can be started. The risk of facial nerve injury in arthrocentesis of the TMJ joint is extremely small [40]. The procedure of injecting adipose tissue is performed through the same needle used during the arthrocentesis. Therefore, the SVF-procedure will not pose any additional risk of nerve injury compared to standard care.

Risks due to the injected product are not expected but can occur because the mechanism of action of SVF is only partly known. Because SVF is such a heterogeneous mixture of cells and the extracellular matrix, its effect is most probably achieved through a variety of mechanisms. The progenitor cells in the tissue can differentiate into cartilage. But the progenitor cells can also have their effect through a paracrine mechanism by excreting anti-inflammatory cytokines, growth factors, or exosomes. It is known that SVF reduces the amount of IL-6 and TNF-alpha [41]. In addition to this, adipose tissue can function as a mechanical protective layer and lubricant, in the same way adipose tissue is used in temporomandibular surgery at the moment. Since the mechanism is not fully known, it theoretically poses the risk of carcinogenesis. The addition of growth factors or immunomodulation is of course reason for concern when there is a chance of tissue differentiating to neoplasms. It is also possible that the immunosuppressive effects at the site of implantation stimulate pre-existing tumours. However, only in vitro studies with expanded ASCs with pre-existing tumour cells have shown that tumour growth is stimulated [42]. We will use non-expanded adipose tissue. In addition to this, tumours of the TMJ are very rare [43]. Therefore, the potential risk of the development of neoplasms is considered negligible.

### 2.8. Sample Size Calculation

To the best of our knowledge, no (pilot) studies have been performed comparing the efficacy of tSVF with only arthrocentesis to treat osteoarthritis of the TMJ. Therefore, we performed a sample size calculation based on the assumption that the difference in mean change between the interventions would be 0.8 for our primary outcome variable (pain during movement).

Regarding the sample size calculation, the following values were used for a longitudinal random effects analysis: α = 0.05, power = 0.80, and an allocation ratio of 1:1 (r = 1). A formula was used from the literature [44], whereby Z(1 − α/2) = 1.96, Z(1 − β) = 0.84, σ = 0.94 (the pooled SD is based on the baseline measurements De Riu [45]), T = 4 follow-up moments, ρ = 0.7 (our estimation of the correlation between observations over time), v = 0.8 (difference in means). This results in a sample size of 16.8 ≈ 17 per group. To compensate for loss to follow-up, we plan to include 20 participants in each group.

### 2.9. Statistical Analysis

Since we are interested in the development of the difference in outcome variables between the groups over time (1 year) and because we assume that missing values may occur due to participants missing appointments, we plan to perform a longitudinal random effects analysis for the primary endpoint. In the secondary endpoint analysis, we will analyse the main effects of group and time as well as the interaction effect of group and time. Differences in these scores between the treatment and control groups will be analysed by the longitudinal random effects model. Cytokine levels will be related to outcome measures of the study by calculating the Pearson correlation coefficient for each outcome measure. Descriptive statistics will be provided for all outcome measurements.

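### The 80% power holds for the pain difference averaged over the four follow-up visits, but 2.8 also calls that 0.8 a mean change and 2.9 motivates the primary model by how the difference develops over time

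*Protocol article*

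**What the plan says.** Section 2.8 sizes the trial for a longitudinal random effects analysis. It first assumes that "the difference in mean change between the interventions would be 0.8 for our primary outcome variable (pain during movement"). When the inputs are listed, the same number appears as "v = 0.8 (difference in means"). The other inputs are "α = 0.05, power = 0.80, and an allocation ratio of 1:1 (r = 1"), "Z(1 − α/2) = 1.96, Z(1 − β) = 0.84", σ = 0.94, ρ = 0.7 and "T = 4 follow-up moments". On the SD, the text says "the pooled SD is based on the baseline measurements". The result is 16.8, rounded to 17 per group, with 20 per group planned to allow for loss to follow-up.

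Section 2.9 gives two reasons for using the same type of model for the primary endpoint. One is expected missing values. The other is "Since we are interested in the development of the difference in outcome variables between the groups over time (1 year"). It does not say which effect from that model is the primary test. For the secondary endpoint analysis it adds that "we will analyse the main effects of group and time as well as the interaction effect of group and time".

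**The concern.** A longitudinal model yields several treatment contrasts: the difference averaged over visits, the difference at one visit, the difference in change from baseline, and the change in the difference over time. They have different variances and answer different questions. Section 2.8 computes power for the first. Its text also describes a change from baseline, and the rationale in 2.9 points to a change over time.

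An average over visits removes the information on how the difference develops. Conversely, a test of development over the follow-up visits ignores any part of the effect that is the same at every visit. An early and lasting benefit is plausible here: the Discussion cites a trial of a related adipose product with pain reduction at 10 days and 1 month. If the benefit then stayed level, a test of development over weeks 3 to 52 would have little chance of showing it. At stake is whether the quoted 80% describes the test that will carry the conclusion.

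**Working it through.** **Inputs (2.8, with the visit schedule from 2.3).** z-values 1.96 and 0.84; σ = 0.94; ρ = 0.7; T = 4; v = 0.8; ratio 1:1; follow-up at weeks 3, 12, 26 and 52. Throughout I assume the same σ at every visit and the same ρ between any two visits, baseline included.

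**General form.** For a contrast whose variance per patient is f·σ²:

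n per group = 2 × (1.96 + 0.84)² × σ² × f / v² = 2 × 7.84 × 0.8836 × f / 0.64 = 21.648 × f

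**Reproducing the plan's figure.** For the mean of four equally correlated follow-ups, f = [1 + (T − 1)ρ]/T = (1 + 3 × 0.7)/4 = 0.775. Then n = 21.648 × 0.775 = 16.78, the stated 16.8. The contrast SD is 0.94 × √0.775 = 0.8275. Power (normal approximation) is 80.5% at 17 and 86.4% at 20 per group. Neither a baseline term nor a time term enters.

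**Other readings of 0.8 with the same σ and ρ.**

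| Contrast | f | n per group | Power at 17 | Power at 20 |
|---|---|---|---|---|
| Average of 4 follow-ups (the plan's formula) | 0.775 | 16.8 | 80.5% | 86.4% |
| Average of 4 follow-ups minus baseline | 0.775 + 1 − 2 × 0.7 = 0.375 | 8.1 | 98% | 99% |
| Change from baseline at one visit | 2 × (1 − 0.7) = 0.6 | 13.0 | 89% | 94% |
| Raw difference at one visit | 1 | 21.6 | 70% | 77% |
| Average of 4 follow-ups, adjusted for baseline | 0.775 − 0.7² = 0.285 | 6.2 | over 99% | over 99% |

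Both change contrasts need fewer patients than planned. The last row shows what baseline adjustment would bring, provided the correlation of 0.7, which 2.8 calls the authors' own estimate, also holds between baseline and follow-up.

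**Group-by-time over the four follow-up visits.** Power depends on the squared deviations of the visit differences from their own mean:

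ncp = (n/2) × Σ(δ_t − mean δ)² / [σ²(1 − ρ)], with σ²(1 − ρ) = 0.8836 × 0.3 = 0.265

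- Constant 0.8: every deviation is 0, so ncp = 0 and power is 5%.
- Difference rising in equal steps from 0.4 to 1.2 (mean 0.8): sum of squares 0.356; ncp = 8.5 × 0.356/0.265 = 11.4; power of the 3-df test is 82% at 17 per group. The averaged test has 80.5%.
- Difference rising in equal steps from 0 to 0.8 (mean 0.4): the sum of squares is again 0.356, so the interaction test keeps 82%, while the averaged test falls to 29%.

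These time patterns are my assumptions; the article gives none. Without one, no power can be attached to a test of development over time.

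**The case against.** The strongest reply is that 2.8 and 2.9 name the same model, that the averaged group effect is a legitimate test within it, and that 80% is right for that test. The sentence in 2.9 gives reasons for choosing a longitudinal model and does not designate a test. The group, time and interaction effects are introduced under the secondary endpoint analysis. A separate analysis plan, not shown, may name the contrast. All of this stands. What remains is in the printed text: one number with two meanings in 2.8, and a rationale in 2.9 pointing to a quantity that 2.8 did not power.

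A reader might infer four stronger things that the article does not support.

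- **That the 80% does not belong to the planned analysis.** It does, if the averaged effect is the primary test.
- **That the trial is underpowered.** A linear group-by-week test over weeks 0 to 52, with 0.8 reached by week 3 and held, has only 51% power at 17 per group. That depends on coding week as a straight line, which the article never states. With visit as a category and baseline included, the same pattern gives ncp = 8.5 × 0.512/0.265 = 16.4 and about 91% power.
- **That the error rate is inflated.** The figure 1 − 0.95² = 9.75% needs two independent tests, either of which could establish success. The plan sets up no such rule.
- **That the mean-change wording means too few patients.** The table shows the reverse.

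**Conclusion.** The point holds as a mismatch of wording between the sample size and the stated aim. The 80% in 2.8 applies to one contrast, the pain difference averaged over four follow-ups, and the arithmetic for it is correct. It is not the power of a mean-change contrast (89% to 98% at 17 per group under the plan's inputs). It is also not the power of a group-by-time test, which is 5% for a constant 0.8 over the follow-up visits and otherwise depends on a time pattern that is not given. The figures rest on σ = 0.94, ρ = 0.7 and equal correlation between all visits. It is worth correcting because it decides which result the 80% supports, but it does not undermine the planned 20 per group.

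**What to change.** In 2.9, name one primary test: the group difference in VAS pain during movement averaged over the follow-up visits, from the longitudinal random effects model with visit as a category and baseline VAS as covariate, two-sided 5%. Keep group-by-visit and the per-visit differences secondary; that still serves the interest in how the difference develops.

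In 2.8, describe v = 0.8 once, as the difference in average follow-up means. State that the 80% is for that contrast without baseline adjustment, and that adjustment raises it under the plan's own correlation of 0.7 (variance factor 0.775 down to 0.285).

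If the authors do want the development over time as the primary question, they should instead state the expected pattern of differences by visit and redo the calculation for it.

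The recommended change costs a few sentences. Baseline VAS is already collected, no patients are added, and 2.2 says approval is still pending, so it can be made now.

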The hypothesized mechanism of action of tSVF in a chronically low-grade-inflamed osteoarthritic joint is that the cells secrete anti-inflammatory factors in a paracrine fashion, which downregulates inflammation. Since the cells will probably not be engrafted in the joint, cartilage regeneration is not expected to occur. Testing this hypothesis is necessary to understand its mechanism of action better. We will therefore test the synovial fluid at both baseline and after 26 weeks for pro-inflammatory and anti-inflammatory factors in both the intervention and the control group. We expect that tSVF will reduce potentially harmful factors such as IL-1B, TNF-alpha, chemoattractants, and MMPs, as well as PGE2, one of the most important factors that maintains the chronic inflammation in the joint. In addition to this, we pose that tSVF, through the secretion of growth factors such as FGF, VEGF, IGF, and HGF, sets the local micro-environment into ‘regenerative mode’ by putting activated synoviocytes into rest mode. There is no synovial fluid analysis data available from TMJ osteoarthritis patients after a tSVF injection. However, in a study of patients with knee osteoarthritis, a reduction in pro-inflammatory molecules (MMP-2, IL-1B, IL-6, and IL-8) and an increase in anti-inflammatory molecules (IGF-1 and IL-10) were found at the 1-year follow-up after an SVF injection [21]. However, performing an additional arthrocentesis for synovial fluid analysis in the recovering joint after 26 weeks to test the mechanism of action for scientific reasons could be considered unethical since there is no benefit for the patient. Nonetheless, because these adipose-derived regenerative treatments are still in their early stages, testing their mechanisms of action is often required to obtain medical ethical approval.

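### The plain Pearson correlation of cytokine levels with outcomes has no stated arm adjustment and suits skewed, variably diluted lavage values poorly, and the between-arm cytokine test is left unclear

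*Protocol article*

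**What the plan says.** Section 2.9 gives cytokines one sentence of their own: "Cytokine levels will be related to outcome measures of the study by calculating the Pearson correlation coefficient for each outcome measure". It mentions no split by or adjustment for arm, no transformation, no time point, and no choice between level and change.

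The same section describes the secondary endpoints in general: "In the secondary endpoint analysis, we will analyse the main effects of group and time as well as the interaction effect of group and time". It continues: "Differences in these scores between the treatment and control groups will be analysed by the longitudinal random effects model". Section 2.1 lists "synovial cytokine analyses at baseline and after 26 weeks" among the secondary endpoints.

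On sampling, Section 2.6 says that at week 26 "an additional arthrocentesis will be performed to acquire synovial fluid for analysis in both the control and intervention group", and that "Synovial fluid will be analysed with a Luminex assay containing pro- and anti-inflammatory factors"; it names 11 analytes. Section 2.5 says that "a maximum amount of 2 mL saline solution will be injected into the superior joint space". The saline drawn back is what goes to the laboratory. The Discussion gives the purpose: "We expect that tSVF will reduce potentially harmful factors such as IL-1B, TNF-alpha, chemoattractants, and MMPs", and PGE2 as well.

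**The concern.** The Discussion's hypothesis is a contrast between arms: tSVF lowers harmful factors relative to arthrocentesis alone. A correlation between cytokine and pain cannot by itself show that.

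The correlation is also hard to interpret as specified. After treatment, arm is a common cause of cytokine level and outcome. Unless arm is adjusted for, two unrelated treatment effects look like a link between cytokine and symptom. Pearson on raw concentrations is also sensitive to a few large values, and a concentration measured in lavage fluid depends on how much saline went in and came back.

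The Discussion concedes that the week-26 arthrocentesis has no benefit for the patient and rests its justification on testing the mechanism. The analysis of that sample should therefore be able to answer the mechanism question. Lavage volumes not noted at sampling cannot be recovered later.

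**Working it through.** **The plan's own figure.** The documents give no figure for the cytokine analysis. The sample size in Section 2.8 reproduces and supplies two inputs:

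n = (1.96 + 0.84)² × 0.94² × 2 × [1 + 3 × 0.7] / (0.8² × 4) = 7.84 × 0.8836 × 2 × 3.1 / 2.56 = 16.78, so 17 per group. An allowance of 15% for loss gives 17 / 0.85 = 20.

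**Inputs.** From Section 2.8: 20 per arm, and a pain shift of 0.8 / 0.94 = 0.85 SD. Using that shift at week 26 is an assumption. The cytokine shift (0.8 to 1.5 SD), the log-SD of concentrations and the dilution noise are also assumptions, because the documents give none of them.

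**1. Correlation created by arm alone.** With no within-arm link and shifts d1 (pain) and d2 (cytokine) in SD units, the expected correlation over both arms is

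r = (d1 × d2 / 4) / √[(1 + d1²/4)(1 + d2²/4)].

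- d2 = 0.8: 0.1702 / √(1.181 × 1.16) = 0.15
- d2 = 1.5: 0.3191 / √(1.181 × 1.5625) = 0.23

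Simulated share significant at two-sided 0.05, 20 per arm:

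| Cytokine shift | Scale | Unadjusted Pearson | Arm-centred |
|---|---|---|---|
| 0.8 SD | raw, skewed (log-SD 1) | 11% | – |
| 0.8 SD | log or normal | 14–15% | about 5% |
| 0.85 SD | normal | 16% | about 5% |
| 1.5 SD | normal | 32% | about 5% |

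The arm-centred results are on the log or normal scale. Heavy skew damps the effect on raw values: at log-SD 2 the unadjusted share is about 8% for a 0.8 SD shift and 11% for 1.5 SD. That is the loss of sensitivity shown in step 2, not a protection.

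The baseline aspirate is drawn before tSVF or saline is injected (Section 2.5), so arm cannot create a correlation with baseline levels.

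**2. Skew.** True correlation 0.5 on the log scale, no arm effect, 40 patients:

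| Log-SD | Power, raw Pearson | Power, log scale |
|---|---|---|
| 0.5 | 90% | about 92% |
| 1 | 80% | about 92% |
| 1.5 | 67% | about 92% |
| 2 | 55% | about 92% |

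The loss is negligible under mild skew and large under strong skew.

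**3. Dilution.** Take a cytokine log-SD of 1, a true correlation of 0.5, and dilution as independent noise with log-SD 0.5 to 1.0. On the log scale the correlation shrinks to 0.5 / √(1 + 0.5²) = 0.45 and 0.5 / √(1 + 1²) = 0.35. Simulated power is 83% falling to 62% for the log-scale, arm-centred correlation, and 65% falling to 39% for raw Pearson. The log scale helps but does not remove the dilution error.

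**4. Is there a between-arm cytokine test?** Sections 2.1 and 2.9 read together say yes: cytokines are a secondary endpoint, and secondary endpoints get group, time and their interaction. Three features cut against this. The sentence on arm differences speaks of scores, which fits questionnaires better than concentrations. Cytokines then get a separate sentence with a different method. Section 2.1 also introduces its list as secondary endpoints for the intervention group. The text does not settle the matter.

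**The case against.** The strongest objection concerns scope. A reader might infer that the plan never tests whether tSVF lowers cytokines. The documents do not support that: taken literally, the secondary-endpoint sentence in Section 2.9 covers cytokines, fluid is collected in both arms at both times, and the Pearson sentence is then an addition. This stands, and only the ambiguity remains.

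It is also fair that the article does not say the arms are pooled, only that it states no split or adjustment. If both shifts are real, the overall correlation is truly non-zero; calling it false presumes that the question is the link within arms. That is the natural reading of a mechanism analysis, but the article does not say so.

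Three further inferences should not be drawn:

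- **Multiplicity.** 11 analytes by 4 or 5 outcomes give 44 to 55 correlations per time point. The article claims no significance threshold for them, and correction is normally left to an analysis plan. The same holds for values below detection.
- **Tight joints.** One might argue that a stiff joint takes less saline and opens less, so that dilution alone creates a correlation with mouth opening. Nothing in the documents says this.
- **Unrecorded volumes.** The article does not say that volumes go unrecorded. It fixes only a maximum and states no correction.

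Skew is a reasonable expectation, but the documents report no distribution. A log transformation could also appear in an analysis plan that is not shown.

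**Conclusion.** The point holds in limited form. The article commits to a named method, Pearson with no stated arm adjustment, and a better one is available at almost no cost. At week 26 the unadjusted correlation is significant in 11% to 32% of trials with no within-arm link, against about 5% when arm-adjusted. This assumes a VAS shift of 0.85 SD and a cytokine shift of 0.8 to 1.5 SD; heavier skew than log-SD 1 brings the figure closer to 5%. Under right skew, raw Pearson has 90% to 55% power against about 92% on the log scale, for a true correlation of 0.5 at log-SD 0.5 to 2. Dilution can vary and would weaken correlations further on either scale.

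The between-arm cytokine comparison is unclear rather than absent. All of this concerns a secondary mechanism analysis; the primary endpoint and the sample size are unaffected.

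**What to change.** 1. Replace the Pearson sentence in Section 2.9. Relate changes in each cytokine from baseline to week 26 to changes in each outcome by Spearman or log-scale partial correlation, adjusted for arm, and label these analyses exploratory.
2. State in Section 2.9 that log cytokine concentrations enter the group-by-time comparison between arms, adjusted for baseline, and that this is the test of the Discussion's hypothesis.
3. Record the injected and recovered lavage volume for every sample at both visits, so that dilution can be corrected at least approximately.

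The cost is a change of wording and two recorded values per sample. The downside is fewer nominally significant correlations. The third item has to be in place before the first patient is sampled.
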